### 2.3. Study Population

The study will include Malaysian women aged 18–49 years with a previous diagnosis of GDM. Exclusion criteria will be the following: pregnant women, recent hospitalisation within the last 6 weeks, and previously diagnosed medical problems (such as type 1 or type 2 diabetes, cancer, and liver or renal disorders). The sample size will be estimated using the mean difference formula [20]. Based on a study that compared dietary intake and metabolomic profile in NGT, prediabetes and metabolomic profile in women post-GDM in Gothenburg, Sweden [14], considering a 95% confidence level and 80% power, a total of 99 subjects will be needed for the study. To account for nonresponse or refusal to participate, an additional 20% of subjects will be required, leading to a minimum of 126 subjects.

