#### 2.5.8. Metabolomic Profile

NMR sample preparation for plasma and urine will be performed according to published protocols [40,41]. About 2 mL of the fasting blood will be collected into lithium heparin tubes, centrifuged at 1500× *g* for 20 min, divided into aliquots, frozen in a liquid nitrogen tank, and stored at −80 °C until further analysis. Subjects will also have to collect mid-stream urine into a urine container. Sodium azide 0.1% will be added to the urine sample to prevent microbial growth. The urine samples will be centrifuged at 1500× *g* for 10 min, divided into aliquots, and stored at −80 °C until further analysis.

Upon thawing, 500 μL of plasma will be vortexed for 1 min, then centrifuged for 2 min at 5000× *g* to remove solid debris. We will transfer 400 μL of plasma supernatant into a 0.5 mL ultra-centrifugal filter and centrifuged at 6000× *g* for 30 min to remove macromolecules, including lipids and proteins. We will mix 200 μL of plasma filtrates with 400 μL of phosphate buffer solution (potassium dihydrogen phosphate Kh_2_Po_4_]) prepared in deuterium oxide (D_2_O) containing 0.1% trimethylsilyl propanoic acid (TSP) and 0.1% imidazole). A total of 600 μL of prepared samples will be transferred to 5 mm NMR tubes. For urine, 400 μL of thawed sample will be added to 200 μL of phosphate buffer solution, then centrifuged at 4800× *g* for 5 min before being transferred to NMR tubes.

The nontargeted metabolomic analysis will be performed using a ^1^H-NMR platform. ^1^H-NMR spectra will be acquired using a 500 MHz NMR spectrometer (Varian Inc., Palo Alto, CA, USA). Spectral data will be preprocessed using Chenomx NMR suite software version 9.0 (Chenomx Inc., Edmonton, AB, Canada) by Fourier transformation, auto-phasing, and auto-baseline correction. Spectral data will be divided into 1000 equal bins, digitised into a table of common integral, and exported as a text file for multivariate data analysis.

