Multivariate data analysis of the processed spectra will be performed using SIMCA-P+ version 15.0 (Sartorius Stedim, Umeå, Sweden) by applying various statistical algorithms including principal component analysis (PCA), partial least square discriminant analysis (PLS-DA), and orthogonal projections to latent structures discriminant analysis (OPLS-DA) to determine differences in metabolites between the three groups. Based on the multivariate data analysis results, parts of the spectra (ppm) responsible for the differences between groups will be quantified using Chenomx software by matching the corresponding peak with the metabolite database. PCA score and loading plots will be drawn in SIMCA-P+ software to validate the data obtained from Chenomx software. Pathway identification will be based on the Kyoto Encyclopedia of Genes and Genomes (KEGG) (Kanehisa Laboratories, Kyoto, Japan).

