#### 2.5.9. Nutritype Signatures

Nutritype signature models will be developed based on the three-step chemometric strategy for nutrimetabonomics [42,43]. In step 1, dietary patterns, as assessed by PCA, will be used to identify the factor scores as described in Section 2.5.3. The factor scores will then be designated as “loadings (VFFQ)”. In step 2, factor scores will be coded to create dummy variables (UFFQ). Positive scores will be coded as class number one, whereas negative scores will be coded as class number two. In step 3, the coded factor scores of each dietary pattern will be regressed against the ^1^H NMR metabolite profile to identify the metabolic phenotypes (“loadings, VNMR”) associated with these dietary patterns using PLS-DA to maximise the separation between T2D and non-T2D groups. The corresponding loading plots from the PLS-DA analyses will determine the significant metabolites we will use to develop nutritype signature models [25]. Chemometric analysis will be performed to produce nutritype signature models using SIMCA-P 15.0+ software (Sartorius Stedim, Umeå, Sweden).

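### PCA plots of metabolites already chosen with the glycaemic-group labels are called validation, but in the same women they cannot support the group differences

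*Protocol article*

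**What the plan says.** The metabolite work in Section 2.5.8 of the protocol article runs in this order.

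1. The processed spectra are cut up: "Spectral data will be divided into 1000 equal bins".
2. PCA, PLS-DA and OPLS-DA are applied to the binned data "to determine differences in metabolites between the three groups", that is, NGT, prediabetes and T2D. The last two methods use the group labels.
3. On the strength of those results, "parts of the spectra (ppm) responsible for the differences between groups will be quantified using Chenomx software", by matching peaks to a metabolite library.
4. Then "PCA score and loading plots will be drawn in SIMCA-P+ software to validate the data obtained from Chenomx software".
5. Pathways are identified from KEGG.

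Section 2.5.9 builds the nutritype models through a further PLS-DA on coded dietary scores: "The corresponding loading plots from the PLS-DA analyses will determine the significant metabolites we will use to develop nutritype signature models". Section 2.1 lists the metabolomic profile associated with T2D and prediabetes as aim (b).

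**The concern.** PCA does not use group labels, so a PCA plot in which the groups fall apart looks like independent confirmation. Here it would not be. The variables offered to the PCA were picked with the labels, in the same women. With 1000 candidates and about a hundred women, some bins differ between groups by chance. A supervised method finds them, and a later plot of those bins shows the chance differences again.

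What is at stake is aim (b). Metabolites and pathways could be reported as validated after a step that noise would usually pass.

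**Working it through.** **Sample size, to set the group sizes.** Section 2.3 says "a total of 99 subjects will be needed for the study", "considering a 95% confidence level and 80% power", and that "an additional 20% of subjects will be required, leading to a minimum of 126 subjects". With three equal groups (an assumption), 99/3 = 33 per group; 33/(1 − 0.20) = 41.25, rounded up to 42; 3 × 42 = 126, which reproduces the stated minimum. Inflating the total gives 99/0.80 = 123.75, or 124, and 99 × 1.20 = 118.8, or 119. The base of 99 cannot be rebuilt, because the article gives no mean difference or SD, but nothing below depends on it.

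**Inputs from the article.** 1000 bins; three groups; selection by supervised analysis on those groups; PCA afterwards in the same women.

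**Inputs assumed and varied.**
- Group sizes: 33/33/33, 42/42/42 or 80/31/15.
- Bin correlation: none, blocks of 10 with r = 0.8, or blocks of 20 with r = 0.9.
- Regions kept: the top 10, 20 or 50 bins by variable importance (VIP) from a two-component PLS-DA, or all bins with VIP > 1.

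**Procedure.** Generate data in which no bin differs between groups, select bins with the labels, run PCA on the selected bins in the same women, and test the first two component scores with Wilks' lambda, Λ = |W|/|T| (within-group over total scatter). The share of generalised variance lying between groups is 1 − Λ. Nearest-centroid accuracy on the two scores stands in for what the eye sees. The comparators are PCA on randomly chosen bins, and PCA of the selected bins in newly generated women. There were 200 data sets per setting, so the Monte Carlo standard error at a true 5% is √(0.05 × 0.95/200) = 1.5 percentage points.

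**Results at 42/42/42, no true difference.**

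| Bins kept and correlation | Separated at p < 0.05, same women | 1 − Λ | Accuracy | Random bins, separated | Selected bins in new women, separated |
|---|---|---|---|---|---|
| Top 20, independent | 100% | 49% | 65% | 5.5% | 5.0% |
| Top 20, blocks of 10, r = 0.8 | 100% | 21% | 50% | 7.0% | 7.0% |
| Top 20, blocks of 20, r = 0.9 | 99.5% | 16% | 47% | 7.5% | 2.5% |
| VIP > 1, blocks of 20, r = 0.9 | 82.5% | 13% | 46% | 5.5% | 6.0% |

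With random bins, 1 − Λ was about 3% and accuracy about 39% in each row; that 39%, not one third, is the yardstick for the accuracy column.

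**All 36 settings.** False separation in the same women was 82-100%. It was 97-100% everywhere except VIP > 1 with the strongest correlation, where it was 82-85%. Random bins gave 3-9% and the selected bins in new women gave 2-8.5%, both near the nominal 5%.

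**Other designs.** A simulation with 126 women (42/42/42 or 75/38/13), latent-factor correlation, the top 20 or 40 bins, and ANOVA of each of the two components at 0.025 gave 89-100% for selected bins and 3-9% for PCA of all bins. A further run keeping the top 20 bins gave 83-100% in the same women, 2-7% in new women and 3-9% for all bins.

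The new-women comparison isolates the cause. The bins and the PCA are the same; only the women who chose the bins are replaced, and the separation goes.

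**The case against.** The strongest reply is that the sentence does not say what the circularity argument needs. Its object is the Chenomx data, not the group differences, and it sets no separation criterion; the tests above are supplied here. It may mean a check of quantification or a search for outlying samples, and PCA can do the latter. This stands, and it is why the point is conditional. On that reading, though, the plot gives no support to the group differences, and it never sets a fitted concentration beside its own spectrum.

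Nor does the sentence name the variables plotted. An all-bin PCA would behave properly (3-9%). But the order of the text, quantification of selected regions and then plots of the Chenomx data, points to the quantified metabolites, and PCA of the processed spectra is already listed as an earlier step.

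A reader might infer three stronger things that the documents do not support.
- That the check can never fail. With strongly correlated bins and a loose cut, 15-18% of null data sets showed no separation, and accuracy there was 46-49% against 36-39% for unselected bins, which is modest by eye.
- That the study has no cross-validation or permutation test. None is named in Sections 2.5.8, 2.5.9 or 2.7, but a condensed article may leave these to a fuller document. The point rests on the step that the article does state.
- That false metabolites pass straight into the nutritype models. Section 2.5.9 makes its own PLS-DA selection, so any effect there is indirect. KEGG mapping is not made conditional on the plot either.

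Finally, the simulations use bins, not library-matched metabolites. Matching follows selection and uses the same women, so it does not undo the selection, but how far it changes the percentages is unknown.

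**Conclusion.** The point holds in conditional form. Read as support for differences between NGT, prediabetes and T2D, the PCA plots are circular: with no true difference they would show separation in about 82-100% of data sets, against about 2-9% when selection and checking are kept apart. Read as a technical check, they can find outlying samples but are no evidence for the group differences or for the concentrations. Either way the word validation promises more than the step delivers.

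The percentages rest on assumed group sizes, bin correlation, number of regions kept and use of VIP for selection. The direction was the same in every setting tried. The consequence falls on aim (b) and the pathway results. It calls for a correction before analysis and does not undermine the study's design.

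**What to change.** In Section 2.5.8:

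- Stop describing the PCA of selected metabolites as validation. Keep it as an illustration or an outlier check, and say which.
- Base any unsupervised statement about group separation on the PCA of all bins, before label-based selection. That PCA is already among the listed analyses.
- Validate the PLS-DA and OPLS-DA group models by cross-validation with bin selection repeated inside each fold, and by permuting the group labels through the whole pipeline, selection included. State the number of folds and permutations in advance.
- Report metabolites and pathways for aim (b) as supported only where the model beats its permutation distribution, and otherwise as exploratory.

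If a fuller document already contains such validation, the article's sentence should be brought into line with it. The cost is a change of wording and some computing time, with no new samples or measurements. The downside is that some separations may not survive.

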#### 2.5.9. Nutritype Signatures

Nutritype signature models will be developed based on the three-step chemometric strategy for nutrimetabonomics [42,43]. In step 1, dietary patterns, as assessed by PCA, will be used to identify the factor scores as described in Section 2.5.3. The factor scores will then be designated as “loadings (VFFQ)”. In step 2, factor scores will be coded to create dummy variables (UFFQ). Positive scores will be coded as class number one, whereas negative scores will be coded as class number two. In step 3, the coded factor scores of each dietary pattern will be regressed against the ^1^H NMR metabolite profile to identify the metabolic phenotypes (“loadings, VNMR”) associated with these dietary patterns using PLS-DA to maximise the separation between T2D and non-T2D groups. The corresponding loading plots from the PLS-DA analyses will determine the significant metabolites we will use to develop nutritype signature models [25]. Chemometric analysis will be performed to produce nutritype signature models using SIMCA-P 15.0+ software (Sartorius Stedim, Umeå, Sweden).

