#### 2.5.3. Dietary Patterns

The study dietitian will administer a semiquantitative food frequency questionnaire (FFQ) adapted from the nationwide Malaysian Adult Nutrition Survey, to determine food consumption in the past month [21]. It contains 14 food groups: grain and cereal products; fast food; meat and poultry; fish and seafood; eggs; legumes, seeds and nuts; milk and dairy products; vegetables; fruits; beverages; alcoholic drinks; confectionaries; bread spread; and condiments. The portion size of the food items will be according to the Food Portion Sizes of Malaysian Foods Album [22]. The amount consumed food will then be converted into grams per day for each food item [10].

Dietary patterns will be derived based on PCA. Data suitability for factor analysis will be assessed prior to performing PCA [23,24]. Food items will be classified based on similarities in nutrient profiles and previous local studies [24,25,26]. The factor scores will be orthogonally rotated by varimax transformation to increase loading differences for easier interpretability [24,27]. Eigenvalue cut-off > 1.5 will determine the number of factors [28]. Food items with factor loadings < ±0.3 will be removed from further analysis [24,28]. A high factor score, whether positive or negative, indicates a high intake of that food group in dietary pattern; and vice versa [23,27].

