### 2.7. Statistical Analysis

Statistical analysis will be performed using SPSS statistical software version 25.0 (IBM, Chicago, IL, USA). Data for categorical variables will be reported as number and percentage, while continuous data will be reported as mean ± standard deviation (SD). Data normality will be assessed prior to data analysis. The study will analyse the differences in the demographic characteristics between subjects who agreed to participate in the study versus those who did not agree to participate. Pearson’s correlation coefficient test will be used to determine correlations between continuous variables, the Chi-squared test to determine the association between categorical variables, and one-way analysis of variance (ANOVA) to compare the differences between the three groups. Multivariate linear regressions will determine the association between the metabolomic profile and factor scores of each dietary pattern yielded from PCA. Multinomial logistic regression will determine the factors, and the nutritype signature models associated with T2D. Variables significant at the bivariate level will be entered into the regression model as confounders. Crude and adjusted odds ratios (ORs) with a 95% confidence interval (CI) will be presented. Subgroup analyses will also be performed, such as early versus late postpartum (<1 year versus ≥1 year post-GDM), supplement versus nonsupplement users, and obese versus nonobese subjects. A previous study found different risk factors of T2D at early (<1 year) versus late postpartum (≥1 year) following GDM [4]. In case of missing data, the study will report the number of available data for the variable. We will analyse any differences in the characteristics between reporters versus nonreporters. A *p*-value < 0.05 for all statistical tests will be considered significant.

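### Splitting each dietary-pattern score at zero before PLS-DA discards information at the step that selects the signature metabolites

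*Protocol article*

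**What the plan says.** Section 2.5.3 derives dietary patterns from the food frequency questionnaire by principal component analysis with varimax rotation ("The factor scores will be orthogonally rotated by varimax transformation"). It treats the size of a score as informative about intake.

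Section 2.5.9 builds the signatures "based on the three-step chemometric strategy for nutrimetabonomics". Step 2 codes each score by sign: "Positive scores will be coded as class number one, whereas negative scores will be coded as class number two". The third step relates these two classes to the NMR data by PLS-DA. The section then states how metabolites are chosen: "The corresponding loading plots from the PLS-DA analyses will determine the significant metabolites we will use to develop nutritype signature models".

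Section 2.7 plans a second analysis of the same relation and does not mention coding: "Multivariate linear regressions will determine the association between the metabolomic profile and factor scores of each dietary pattern yielded from PCA".

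Section 2.1 names the nutritype signatures associated with T2D as the primary outcome, and aim (c) is the association between dietary patterns and the metabolomic profile.

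**The concern.** A dietary-pattern score is a graded measure. Cutting it at zero puts women with almost identical diets, just either side of the average, into opposite classes. It also merges women with a weak pattern and women with a very strong one. Those near zero contribute mostly noise to the class contrast, and those in the tails lose the extra weight that their diets should carry.

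The place where this happens matters. The PLS-DA on the coded scores selects the metabolites, the selected metabolites form the signature models, and those models enter the multinomial regression for T2D. Information lost at the split cannot be recovered later in that chain. In a study of this size, a weaker selection step means more diet-related metabolites missed and a less stable signature.

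A second matter follows from it. Section 2.7 relates the same metabolites to scores that appear to be uncoded, so the article may report two answers to aim (c) that differ.

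**Working it through.** **Inputs from the protocol article.** Cut at zero into two classes (2.5.9); base sample size 99, 80% power and 95% confidence (2.3); final minimum 126 after a 20% allowance (2.3); significance level 0.05 (2.7).

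**Assumptions, because the article does not give them.** Scores have mean zero; tests are two-sided; each metabolite is linear in the score. The score distribution is varied below.

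**1. The plan's own sample size.** Inflating the total gives 99 / (1 − 0.20) = 123.75, so 124. Inflating three assumed groups of 33 gives 33 / 0.80 = 41.25, so 42 per group and 3 × 42 = 126, which matches. The base of 99 cannot be recomputed, because no effect size or SD is given. Both 99 and 126 are carried forward, since 126 includes the allowance for non-response.

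**2. Information kept by the split.** For a normal score cut at c, with a proportion p in one class, the efficiency relative to the continuous score is φ(c)² / [p(1 − p)]. At c = 0 and p = 0.5:

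(1/2π) / 0.25 = 2/π = 0.637, a loss of 36.3%.

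- 126 × 0.637 = 80 effective women
- 99 × 0.637 = 63 effective women

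**3. Other score shapes, each split at its mean.** The loss is 1 minus the squared correlation between the score and its class code.

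| Score shape | Share above zero | Loss |
|---|---|---|
| Uniform | 50% | 25% |
| Normal | 50% | 36% |
| Right-skewed (gamma, exponential, lognormal) | 37% to 43% | 38% to 43% |
| Heavy-tailed, t with 5 df | 50% | 46% |

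**4. Illustrative power, one metabolite.** The split multiplies the correlation by √(2/π) = 0.798. By the Fisher z approximation, power is about Φ(atanh(r)·√(N − 3) − 1.96). For r = 0.25 and N = 126:

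- continuous: 0.2554 × 11.09 − 1.96 = 0.87, power 81%
- split: r becomes 0.199; 0.2022 × 11.09 − 1.96 = 0.28, power 61%

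| r, N = 126 | Continuous | Split |
|---|---|---|
| 0.20 | 61% | 43% |
| 0.25 | 81% | 61% |
| 0.30 | 93% | 77% |

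At N = 99, a correlation of 0.28 has 80% power on the continuous score and about 60% after the split.

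**5. How often the two analyses differ.** In 10,000 simulated studies per setting (normal scores, one metabolite), the continuous and split analyses differed on significance at 0.05 as follows, for N = 126:

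| True r | Differ | Only continuous significant | Only split significant |
|---|---|---|---|
| 0 | 5.7% | 2.9% | 2.8% |
| 0.20 | 26.4% | 22.6% | 3.7% |
| 0.25 | 23.2% | 21.0% | 2.2% |
| 0.30 | 17.5% | 16.7% | 0.8% |

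At N = 99 the figures for r = 0.20 to 0.30 lie between 21% and 26%. The analyses agree in most runs. Where they differ under a true association, it is mainly because the split analysis misses it.

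**The case against.** **The coding follows a published strategy.** Section 2.5.9 cites it, and comparability with earlier work is a legitimate reason to keep it. This stands as a reason for the choice, but citing a template does not restore the information, and the article does not say why these scores need to be binary.

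**The plan does say what defines the signature.** A reader might infer that there is no rule for choosing between the two analyses. The text does not support that, because section 2.5.9 gives metabolite selection to the PLS-DA loading plots. Only the handling of a discordant linear regression is unstated, which is a smaller gap.

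**The two analyses need not conflict.** A discriminant model for selection and a regression for estimating association can complement each other. This stands: disagreement is a possibility, and mostly the same loss of power seen from another side.

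**The study as a whole does not lose this information.** This also stands. The regression in section 2.7 appears to use the uncoded scores, so the loss belongs to the signature step alone.

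**The power figures do not model the planned step.** PLS-DA works on many spectral bins at once, and no per-metabolite test at 0.05 is stated for it. The figures show direction and rough size; they are not the power of the signature model.

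**The response is not wholly clear.** Step 3 also describes PLS-DA as separating T2D from non-T2D women. The calculation takes the coded dietary score as the response, which is what the first part of that sentence says.

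**Conclusion.** The point holds for the PLS-DA step in section 2.5.9. Coding each dietary-pattern score by sign discards information exactly where the primary-outcome metabolites are selected.

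The loss is about 36% if scores are near normal and between about 25% and 46% over the shapes examined. The normal-score figure rests on an assumed distribution and on a linear relation between each metabolite and the score; neither is given in the article. The fall in power is an illustration for a single metabolite.

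It would go too far to say that the plan contradicts itself or that the two analyses will give conflicting answers. They may disagree: for one truly associated metabolite of moderate size, roughly one simulated study in six to one in four did so, and PLS-DA remains the stated selecting step.

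**What to change.** Reword steps 2 and 3 of section 2.5.9 so that the continuous factor score of each dietary pattern is the response in PLS or OPLS regression on the NMR profile, and so that this model selects the signature metabolites. The selection step would then use the same form of the score as the linear regression in section 2.7 appears to use.

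Keep the two-class coding for score-plot display, or as a sensitivity analysis that allows comparison with the cited strategy. State in one sentence that the continuous-score model governs if the analyses differ. The same edit can make clear that the dietary score, and not T2D status, is the response in step 3.

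The cost is a change of wording. No new data or measurements are needed, and PLS-DA is itself PLS with a class-coded response, so the planned software should serve. The downside is a small departure from the cited three-step template, which the sensitivity analysis largely covers.

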### 2.4. Recruitment

Women who fit the selection criteria will be invited to join the study. Subjects will then be selected using systematic random sampling. Informed written consent will be obtained at enrolment. Subjects will be briefed on the benefits and potential risks of joining the study.

Subject recruitment commenced in March 2021, and enrollment is expected to continue through October 2022. The research workflow is shown in Figure 1.

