#### 2.5.2. Sociodemographic Characteristics and Obstetric History

The study will collect sociodemographic data on age, ethnicity, education level, marital status, occupation, household income, and household size using a structured questionnaire. A family history of diabetes will also be assessed. Information on obstetric history will be obtained from the antenatal records. This will include gravidity, parity, pre-pregnancy weight, gestational weight gain, postpartum weight retention, number and timing of GDM diagnosis, duration lapse since GDM diagnosis, treatment during GDM, delivery method, birth outcomes, infant birth weight, breastfeeding duration, and family planning.

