Metabolomic profiles associated with dietary patterns have been previously studied in women post-GDM [14,15,16,17]. In the study by Andersson-Hall et al. involving 237 Scandinavian women post-GDM, linoleic acid was positively associated with vegetable oil and negatively associated with margarine intake. The linoleic acid level was reduced in women post-GDM who transitioned to T2D [14]. However, food intakes were calculated as the proportion of total diet (%) and not their absolute values in the study [14]. Another study involving 347 women post-GDM from the Nurses’ Health Study II found a correlation between dietary and plasma BCAAs [17]. Additionally, women post-GDM with higher dietary and plasma BCAAs had an elevated risk of T2D [17]. Serum and dietary polyunsaturated fatty acids were also correlated in the German study by Fugmann et al.; however, this study did not correlate dietary and serum fatty acids with the risk of T2D [15]. One study did not find any association between dietary glycaemic index and metabolites and did not assess the correlation between these parameters with the risk of T2D [16]. All of these studies [14,15,16,17] only focused on specific types of food or dietary components, instead of exploring dietary patterns as a whole. Only two studies [14,17] directly associated dietary intake and metabolites with the risk of T2D, indicating a paucity of evidence concerning nutritype signatures. Furthermore, all of these studies were conducted in the Western population, whose metabolomic profile may differ from that of the Asian population [49]. For instance, White European pregnant women had significantly lower glucose levels and most amino acid metabolites compared with South Asians, due to differences in body mass index and characteristics during pregnancy [49].

This study has a few limitations. The nature of the study is cross-sectional. Hence, the study will not be able to establish causation and effect. The study is limited to exploring only associations between dietary patterns, metabolomic profile, nutritype signatures, and T2D at a single time point. We also will not stratify subjects according to whether they have been practising certain treatments for T2D.

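### Ethnicity is recorded but left out of the PLS-DA that selects the nutritype metabolites, and it can reach the later regressions only through a p<0.05 screen, so part of a signature could reflect ethnic group rather than diet

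*Protocol article*

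**What the plan says.** - **Population and sampling.** Section 2.3: "The study will include Malaysian women aged 18–49 years with a previous diagnosis of GDM". Section 2.4: "Subjects will then be selected using systematic random sampling". Neither section sets an ethnic restriction, quota or stratum.
- **Ethnicity is measured.** Section 2.5.2: "The study will collect sociodemographic data on age, ethnicity, education level, marital status, occupation, household income, and household size".
- **Diet patterns.** Section 2.5.3: "Dietary patterns will be derived based on PCA", with varimax rotation. No ethnic strata are mentioned.
- **Building the nutritype.** Section 2.5.9 first codes each score by sign: "Positive scores will be coded as class number one, whereas negative scores will be coded as class number two". Then "the coded factor scores of each dietary pattern will be regressed against the" NMR metabolite profile by PLS-DA, and the loading plots decide which metabolites form the signature. No covariate or stratum appears in these steps.
- **The only adjustment rule.** Section 2.7: "Variables significant at the bivariate level will be entered into the regression model as confounders". The significance level is 0.05 for all tests. The section does not say against which outcome a variable is screened, or whether the rule covers the linear models as well as the multinomial one. Ethnicity is not among the example subgroups.

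**The concern.** The article treats a nutritype as the imprint of diet on metabolites. Aims (c) and (d) and the primary outcome in Section 2.1 rest on that link. If ethnic groups differ in what they eat and also, for other reasons, in their metabolite levels, pooling them creates a diet-metabolite correlation that exists within no group. A PLS-DA without ethnicity cannot tell the two apart. Cross-validation does not help, because the same confounding is present in every fold.

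The order of the steps matters. The screen in Section 2.7 belongs to the SPSS regressions, whereas the metabolites are chosen in the SIMCA PLS-DA of Section 2.5.9. Even if ethnicity passes the screen, it does so in models that play no part in that choice. A significance screen is also a weak way to choose confounders, since a variable can confound without reaching p<0.05 in a sample of this size.

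**Working it through.** **The plan's own figure.** 99 subjects is 33 per group in three groups. 33/(1-0.2) = 41.25, rounded up to 42, and 3 × 42 = 126. So n = 126 is reproduced and is used below.

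**Assumptions (not in the article).** A minority share p; the minority's mean diet score shifted by d and its mean metabolite level by m, both in within-group SD; no diet-metabolite link inside either group; two-sided 5% tests.

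**Correlation created by pooling**

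r = p(1-p)·d·m / √{[1 + p(1-p)d²]·[1 + p(1-p)m²]}

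**Chance of a significant unadjusted result**

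z = √(126-3) × atanh(r) = 11.09 × atanh(r); rate = Φ(z-1.96) + Φ(-z-1.96)

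Worked case, p = 0.4, d = 1, m = 0.8: the numerator is 0.24 × 0.8 = 0.192 and the denominator √(1.24 × 1.1536) = 1.196. So r = 0.161, z = 1.80 and the rate is 43.5%.

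| p | d | m | r | rate |
|---|---|---|---|---|
| 0.3 | 0.3 | 0.3 | 0.019 | 5.5% |
| 0.1 | 1 | 0.5 | 0.043 | 7.6% |
| 0.1 | 1 | 0.8 | 0.067 | 11.6% |
| 0.3 | 0.5 | 0.5 | 0.050 | 8.6% |
| 0.4 | 0.5 | 0.5 | 0.057 | 9.6% |
| 0.3 | 1 | 0.5 | 0.093 | 17.9% |
| 0.4 | 1 | 0.8 | 0.161 | 43.5% |

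Simulation gave 19% and 41% where the last two rows give 17.9% and 43.5%, and 6-8% with 0.3 SD shifts or a 10% minority. The formula uses the continuous score, as in the linear regressions. Coding by sign discards information and lowers the rates somewhat.

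**Three-group check with the sign split** (2,000 runs per setting, group means at -s, 0 and +s). At a 60/25/15 mix the unadjusted rate was 7% with shifts of 0.3 SD in both, 21% with 0.5 in both, 35% with 0.8 diet and 0.5 metabolite, and 69% with 0.8 in both. In the last case the outer groups lie 1.6 SD apart. At 85/10/5 the four rates were 6%, 7%, 13% and 21%. With ethnicity as a covariate the rate was 4-6% in every setting.

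**Whole-model check.** A two-component PLS-DA (150 features, 7-fold cross-validation, 39 permutations) found a diet signature in 21-56% of data sets with a 30-40% minority, a 1 SD diet shift and 20% of features shifted by 0.5-0.8 SD. After residualising on ethnicity the rate was 5-9%. A separate rebuild gave 29% for 30% minority, 1 SD diet and 0.5 SD metabolite. Milder settings gave far less: 8% with both shifts at 0.5 SD, 4% with both at 0.3 SD, 6% with a 10% minority, and 9% with 5% of features shifted.

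**Does the screen let ethnicity in?** Take n = 126 and a 30% minority (37.8 against 88.2 women).
- *Against diet score or metabolite.* SE = √(1/37.8 + 1/88.2) = 0.194. For 1 SD, 1/0.194 = 5.14 and admission is 99.9%. For 0.5 SD, z = 2.57 and admission is about 72%. For 0.8 SD, z = 4.12 and admission is about 98%.
- *Against T2D, 8% vs 16%.* The pooled rate is 0.7 × 0.08 + 0.3 × 0.16 = 0.104, and SE = √(0.104 × 0.896 × 0.0378) = 0.0593. So z = 0.08/0.0593 = 1.35 and admission is Φ(1.35-1.96) ≈ 27%. Direct calculation over 30-40% minority gives 29-32%.
- *Against T2D, 8% vs 20%.* Direct calculation gives 51-55%.

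**The case against.** **The screen may work.** For a diet-metabolite regression the natural bivariate tests are ethnicity against the diet score or against the metabolite. When shifts are large enough to matter, these usually admit ethnicity, and simulation of the screened linear regression gave false-positive rates of 4-5%. This stands: it would be wrong to infer that the later regressions generally miss ethnicity. It does not rescue the PLS-DA, which the screen never reaches, and Section 2.7 leaves a screen against T2D equally possible.

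**The evidence is not about this sample.** A reader might take the Discussion to show that Malaysian ethnic groups differ in diet and metabolites. It does not. The diet statement contrasts Malaysians with Caucasians. The metabolite statement, "White European pregnant women had significantly lower glucose levels and most amino acid metabolites compared with South Asians", concerns pregnant women in a Western-Asian contrast, and the article attributes the difference to body mass index and characteristics during pregnancy. A multi-ethnic sample is itself an inference from ethnicity being recorded and no restriction being set. This stands, and it makes the point conditional.

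**Adjustment can remove real signal.** If groups eat differently and their metabolites differ because of it, residualising on ethnicity deletes part of the nutritype. The simulations assume no true link within groups, so they cannot measure that loss. This stands, and it argues against replacing the planned PLS-DA.

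**Covariates may be in a fuller plan.** Covariate lists are often left out of an article, and other variables could be named too. But this article states both the metabolite-selection rule and the confounder rule. The point concerns those stated rules.

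**Conclusion.** The point holds as a conditional weakness in a stated method. Ethnicity is available, is absent from the step that selects the signature metabolites, and can enter later models only through a screen with an unspecified outcome. If the sample is mixed and both diet and metabolites differ by group, part of a signature can be ethnic.

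The size rests wholly on the assumed mix and shifts. At n = 126 with no within-group link, the unadjusted per-metabolite false-positive rate is about 6% with 0.3 SD shifts, and 6-8% with a 10% minority, 1 SD in diet and 0.5 SD in metabolite. It rises to about 41% (43% by the formula) with a 40% minority, 1 SD in diet and 0.8 SD in metabolite. Adjusted, it is about 5%. A T2D-based screen admits ethnicity in about 30% of samples at 8% vs 16%, and in 51-55% at 8% vs 20%. A screen on diet or metabolite usually admits it when shifts are large.

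A reader might go further and conclude that the signatures will be ethnic markers. The documents do not support that: they give no ethnic mix and no within-Malaysia differences, and with one dominant group or small shifts the effect is close to nominal.

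**What to change.** 1. In Section 2.7, name ethnicity as a forced covariate in the linear and multinomial models whatever its p value, with small categories grouped.
2. In Section 2.5.9, keep the planned PLS-DA and report beside it a second PLS-DA on diet scores and NMR features residualised on ethnicity.
3. Check the signature within the largest ethnic group.
4. Label as ethnicity-dependent any metabolite that does not persist in these checks.

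The cost is analysis wording, one extra preprocessing step on data already collected, and 2-3 degrees of freedom. The adjusted version may lose some true diet signal where diet and ethnicity overlap, which is why both versions should be shown.
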